# CAPAbility: comparison of the JOURNEY II Bi-Cruciate Stabilised and GENESIS II total knee arthroplasty in performance and functional ability: protocol of a randomised controlled trial

**DOI:** 10.1186/s13063-020-4143-4

**Published:** 2020-02-24

**Keywords:** Total knee arthroplasty, Knee replacement, Functional ability, Knee prosthesis, Kinematics, Primary osteoarthritis

## Abstract

**Background:**

Osteoarthritis of the knee is a common condition that is expected to rise in the next two decades leading to an associated increase in total knee replacement (TKR) surgery. Although there is little debate regarding the safety and efficacy of modern TKR, up to 20% of patients report poor functional outcomes following surgery. This study will investigate the functional outcome of two TKRs; the JOURNEY II Bi-Cruciate Stabilised knee arthroplasty, a newer knee prosthesis designed to provide guided motion and improve knee kinematics by more closely approximating a normal knee, and the GENESIS II, a proven existing design.

**Aim:**

To compare the change in Patient-reported Outcome Measures (PROMs) scores of the JOURNEY II BCS and the GENESIS II from pre-operation to 6 months post operation.

**Methods:**

CAPAbility is a pragmatic, blinded, two-arm parallel, randomised controlled trial recruiting patients with primary osteoarthritis due to have unilateral TKR surgery across two UK hospitals. Eligible participants (*n* = 80) will be randomly allocated to receive either the JOURNEY II or the GENESIS II BCS knee prosthesis. Baseline measures will be taken prior to surgery. Patients will be followed at 1 week, 6 to 8 weeks and 6 months post-operatively. The primary outcome is the Oxford Knee Score (OKS) at 6 months post-operatively. Secondary outcomes include: other PROMs, biomechanical, radiological (computerised tomography, (CT)), clinical efficacy and safety outcomes. An embedded qualitative study will also investigate patients’ perspectives via interview pre and post surgery on variables known to affect the outcome of TKR surgery. A sub-sample (*n* = 30) will have additional in-depth interviews to explore the themes identified. The surgeons’ perspectives on the operation will be investigated by a group interview after all participants have undergone surgery.

**Discussion:**

This trial will evaluate two generations of TKR using PROMS, kinematic and radiological analyses and qualitative outcomes from the patient perspective.

**Trial registration:**

International Standard Randomised Controlled Trials Number Registration, ID: ISRCTN32315753. Registered on 12 December 2017.

## Introduction

### Background and rationale

Osteoarthritis of the knee is a common musculoskeletal condition. The surgical management of painful, end-stage osteoarthritis is by total knee replacement (TKR) which should be considered before there is prolonged and established functional limitation and severe pain [1]. Over 100,000 TKRs were performed in the UK in 2019 [2]. While TKR frequently reduces pain and improves physical function in the majority of patients, 20% of patients report poor functional outcomes post-operatively [3, 4]. Such poor outcomes are of importance to patients and have a considerable financial and service-provision impact on NHS care. Research is needed to improve post-arthroplasty outcomes for those patients.

There is a paucity of literature regarding the kinematic outcomes of patients following TKR. However, there is uncertainty as to whether good Patient-reported Outcome Measures (PROMs) are associated with a return to normal kinematics of the TKR knee compared to the native knee. Movement analysis can be used to examine the change in kinematics before and after TKR by examining functional movements in activities of daily living.

The long-term success of TKR depends largely on correct component alignment and accurate ligamentous balancing [5]. The impact of femoral- and tibial-component rotation on flexion-gap balance, patellofemoral tracking and normal kinematic function is well-known [6–8]. Complications secondary to poor component alignment have been reported to lead to a higher rate of revision surgery [9, 10]. Computerised tomography (CT) imaging is a valid and reproducible technique for accurately measuring TKR-component rotation [11, 12]. However, despite CT being widely used to examine implant rotation, the correlation between rotational alignment, PROMs and kinematic function comparing pre- and post-operative measurement is unclear [13, 14]. It is hypothesised that patients with poor rotational profile post-operatively compared to their pre-operative values will have significantly worse PROMs, movement parameters and patient satisfaction.

We report the protocol of a two-group, parallel randomised controlled trial (RCT) comparing patient-reported, surgical and biomechanical outcomes from a TKR of a newer design (the JOURNEY II Bi-Cruciate Stabilised knee arthroplasty (BCS)) designed to provide improved kinematic outcomes compared to an older design TKR implant (the GENESIS II).

This protocol (version 2.4, dated 27 February 2019) has been written and reported according to the Standard Protocol Items: Recommendations for Interventional Trials (SPIRIT) guidance and Checklist [15] (see Additional file 1: SPIRIT 2013 Checklist).

### Aims

The principal aim of the trial is to compare the change in PROMs scores of the JOURNEY II BCS knee and the GENESIS II knee from pre-operation to 6 months post operation. Additional aims are as follows:
To determine whether the temporal and spatial parameters of gait, the range of movement and static and dynamic balance are closer to aged-matched normative data in those receiving the JOURNEY II BCS compared to those receiving the GENESIS II kneeTo monitor the change in function (Aim 1 above) and PROMs of the JOURNEY II BCS and the GENESIS II knee from post operation to 6 months post operationFrom CT scan measures, determine anatomical landmarks and rotational profile around the native knee and following TKR to ascertain the component rotational position post-operatively compared to anatomical landmarksTo examine the relationship between rotational values determined by CT scanning with pre- and post-operative PROMs and movement analysisTo develop knowledge and understanding of patient and surgeon experiences, perspectives and satisfaction when receiving or implanting the JOURNEY II BCS compared with the GENESIS II knee, and their experiences of recovery and rehabilitation

## Methods: participants, interventions and outcomes

### Trial design

This is a pragmatic, triple-blinded, parallel, superiority, randomised controlled trial of the JOURNEY II BCS (intervention) versus GENESIS II (control) in patients with primary osteoarthritis undergoing TKR. Embedded in the clinical trial is a qualitative investigation of participants’ confidence in the TKR received and their experiences of the recovery process in the first 6 months after surgery. The aim of this is to identify any differences in the experience of recovery between each type of TKR. Surgeons will also be interviewed to investigate their perceptions of the surgery and patient’s rehabilitation.

The trial outline is illustrated in Fig. 1.

**Fig. 1 Fig1:**
[figure not shown]
Comparison of the JOURNEY II Bi-Cruciate Stabilised and GENESIS II total knee arthroplasty in performance and functional ability (CAPAbility) trial outline

### Study setting

Trial sites were pre-selected on the basis of their locality to facilitate data collection (namely the kinematic assessment). Sites include the Norfolk and Norwich University Hospital (NNUH), where all patients recruited to the trial will be referred for consideration of TKR. The NNUH refers a proportion of its TKR patients to Spire Norwich where the operation and follow-up physiotherapy is delivered. Both hospital are participating in this trial. All CT scans will be performed at NNUH. The biomechanical assessment will be undertaken in a specialist movement analysis laboratory (MoveExLab) at the University of East Anglia (UEA).

### Eligibility criteria

To be eligible for the trial, patients must satisfy the surgeon’s general requirements for a TKR, meet all inclusion criteria and none of the exclusion criteria listed in Table 1.

**Table 1 Tab1:** Eligibility criteria

Inclusion criteria	
• Listed for a primary TKR at the NNUH (may be referred to Spire Norwich for the operation)	
• Indication for the TKR is primary osteoarthritis of the knee joint involving one or more compartments	
• Aged 18 years or over	
• Patient willing to provide full informed consent to the trial including consent for any incidental findings to be communicated to their general practitioner (GP)	
Exclusion criteria	
• Listed for a single-stage, bilateral TKR procedure	
• Severe symptoms in the contralateral knee so as to require staged, bilateral knee replacements within 6 months of the primary procedure	
• Fixed-flexion deformity of 15° or greater or patients who may require excessive resection of the distal femur	
• Clinically assessed uncorrectable varus/valgus deformity of 15° or greater	
• Any co-morbidity which, in the opinion of the investigator, is severe enough to present an unacceptable risk to the patient’s safety	
• Inflammatory arthritis	
• Previous septic arthritis in the affected knee joint	
• Previous surgery to the collateral ligaments of the affected knee	
• A contralateral TKR that has been implanted less than 1 year from the date of consultation, or severely painful	
• Patients taking warfarin or Novel Oral Anti-Coagulants	
• Will not be resident in the catchment area for NNUH for at least 6 months post surgery	
• Undertaking the surgery as a private (non-NHS) patient	
• Patients who, in the opinion of the clinical staff, do not have capacity to consent	
• Patients who are pregnant	
• Unable to understand written and spoken English	
• Patients currently enrolled on an interventional trial involving surgery, exercise or rehabilitation. Patients can be co-enrolled into studies not meeting the above criteria given prior agreement from the TMG of both studies. Patients who enter the study are eligible for entry onto the National Joint Registry and in terms of the Journey II BCS, into Beyond Compliance	

Patients will be excluded if they are currently enrolled on an interventional trial involving surgery, exercise or rehabilitation. Patients can be co-enrolled into studies given prior agreement from the Trial Management Group (TMG) of both studies. Patients who enter the study are eligible for entry onto the UK National Joint Registry.

### Screening

Potential participants will be approached via a single route. Potential participants will be screened by a member of the clinical team in collaboration with research nurses after having been added to the orthopaedic clinic waiting list. Potentially eligible patients who meet the eligibility criteria will either be handed a Patient Information Sheet (PIS) if still at the clinic, or be posted an invitation letter informing them that the trial is taking place and include the PIS. After having been provided the trial PIS, potential participants will be telephoned by a research nurse. To minimise the possibility of attrition, appointments for outcome measures will be agreed with participants when they enter the trial. In addition, members of the research team will maintain regular contact with participants to ensure attendance at follow-up visits and to monitor any adverse events (AEs).

### Informed consent

Written informed consent to enter and be randomised into the trial will be taken by a member of the clinical team and obtained from participants after explanation of the aims, methods, benefits and potential hazards of the trial. Potential participants will be given as much time as they need to consider whether or not to provide informed consent. Consent will take place before any trial-related measures, at a time convenient to the potential participant, preferably at a time to combine with one or more of the measures to reduce participant visits.

If a participant withdraws prior to surgery, an additional participant will be randomised to ensure that 80 participants complete the surgery.

Patients who, in the opinion of the clinical team, do not have capacity to consent, will be ineligible. If a participant loses capacity during the course of the trial, they will be withdrawn from any further assessments, but any data already collected will be retained. Consent will be re-sought if new information becomes available that affects the participant’s consent in any way. This will be documented in a revision to the PIS and the participant will be asked to sign an updated consent form. These will be approved by the Ethics Committee prior to their use. A copy of the approved consent form is available from the Norwich Clinical Trials Unit (NCTU).

### Sample size

Eighty patients will be recruited onto this superiority trial. The sample size has been calculated from the Oxford Knee Score (OKS) [16]. The OKS ranges from a score of 12 to 60, with 12 being the best outcome. The minimally important clinical difference for OKS is 5 [17, 18] and a standard deviation of 7.4 [19]. For an 80% power, and an assumed dropout rate of 10%, 80 participants will be randomised to one of the two groups.

### Participant timeline

The participant timeline is shown in Fig. 1. Where possible, trial visits will be combined with standard clinic visits. Should additional visits be necessary, participants will be reimbursed for travel costs.

### Interventions

All participants will receive routine care provided by the NHS. Pre-operative and peri-operative care is standardised irrespective of implant.

### Explanation for choice of comparators (Genesis II versus JOURNEY II BCS)

The GENESIS II TKR system made by Smith and Nephew (Smith and Nephew plc, Watford, UK) is frequently used in standard practice within the NHS [2]. It has been the standard TKR within the NNUH and Spire Norwich Hospitals for over 10 years. The Genesis II has a survivorship of over 93% of implants at 15 years [2, 20] and offers good health-related quality of life outcomes [21].

A newer device, JOURNEY II BCS, also manufactured by Smith and Nephew, has been developed to theoretically provide improved kinematic outcomes compared to the GENESIS II [22]. These improvements are proposed to include:
Alteration in the dimensions of the femoral component to reduce soft-tissue strain and maintain more natural translation and external rotationReduction in the thickness of the lateral and medial anterior flange of the femoral component and edge tapering to reducing tension on the iliotibial band (ITB) and iliotibial-patellar bands (ITPB)Reduction in the width of the femoral component to limit implant overhang, and reduction in the mid-flexion thickness of the medial condyle to maintain more consistent strain on the medial collateral ligament (MCL) throughout the flexion rangeA superior cam position, which serves to decrease femoral rollback in the targeted ranges of motion, increase femoral external rotation, and lower the point of tibial post contact in deep flexion

While there is fluoroscopic data to support normal kinematics in early and late flexion [23], there is a paucity of evidence exploring these hypotheses for this newer implant.

### Surgical flow and training

Surgeons will be high-volume arthroplasty surgeons who work at both NNUH and Spire Norwich Hospital. The standard implant at both sites is the Genesis II TKR system. All surgeons have used this implant for many years and are very familiar with the surgical technique. All surgeons and theatre staff have received training on the implantation of the JOURNEY II BCS implant. All surgeons have undergone training on the JOURNEY BCS II implant in a cadaveric laboratory and have also undertaken a learning curve with the device until they were confident with the technique. This was supported by a Smith and Nephew representative. There are minimal differences in the surgical cuts and technique between the Genesis II and the JOURNEY BCS II. Participating surgeons felt that there was a shallow learning curve to the JOURNEY BCS II. Both devices are CE-marked and will be used within indication. Smith and Nephew are providing the JOURNEY II BCS at the same price as the GENESIS II system for this study.

### Surgical procedures

Devices will be identified and prepared for the operation by a surgical technician at the surgery site.

Participants allocated to the intervention device will receive the JOURNEY II BCS prosthesis while participants allocated to the control condition will receive the GENESIS II prosthesis. The type of device implanted and its serial number will be recorded on the trial database, by an unmasked member of the research team.

The surgical procedure will follow the standardised surgical approach and technique. It will be undertaken through a medial parapatellar approach. In both implants and in every case to ensure standardisation of technique, a posterior stabilised prosthesis with patella resurfacing will be used.

It is possible that a decision will be taken prior to, or during, the operation not to use the allocated device if, in the opinion of the surgeon, the patient is found to have become unsuitable for continued participation in the trial. The reasons for an allocated device not being used will be recorded on the trial database. In this case or if a participant chooses to withdraw consent for treatment, or follow-up, all data collected up to the point of withdrawal will be retained. The standard Norwich Enhanced Recovery Programme (NERP) [24, 25] is used for the anaesthetic technique and post-operative recovery.

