### Blinding (masking)

It is not possible to blind the surgeon to the trial intervention. However, the participants, the physiotherapists and all staff involved in assessing outcomes will be blinded. Processes will be in place to maintain blinding. These will include concealment in a sealed envelope of the surgery notes mentioning the prosthesis implanted in the patient file.

In the unlikely event of a research nurse accidentally becoming unmasked, the contacts, assessments and data entry for that participant will be undertaken by another member of the research team for the remaining period of trial participation for that participant. Accidental unmasking will be logged and monitored to ensure that the appropriate steps are taken to prevent a re-occurrence.

The clinical staff providing usual care will also be blinded. The decision to unmask a case will be made when knowledge of an individual’s allocated treatment is required to enable treatment of a serious adverse event (SAE) which is likely to be caused by the type of device implanted.

Where possible, requests for emergency unmasking of individuals will be made via the trial manager in agreement with the clinical chief investigator. However, in circumstances where there is insufficient time to make this request or for agreement to be sought, the treating clinician can make the decision to unmask immediately. This can be done via the trial database.

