### Statistical analysis

A full Statistical Analysis Plan (SAP) will be developed between the trial statistician and chief investigators and agreed with the trial’s Governance Committees. All analysis will be based on the intention-to-treat principle in which all participants will be analysed according to the group to which they were allocated, regardless of compliance.

Baseline factors will be summarised by group. All continuous variables will be summarised by the mean and SD, or if appropriate, the median and interquartile range. Categorical variables will be summarised with the number and percentage, in each category.

The primary comparison for OKS will be made using a general linear model with the stratification factors included as fixed effects. The difference between arms will be summarised using the mean difference, with 95% confidence intervals presented. A similar analysis will be undertaken for all other outcome measures.

For the temporal gait parameters and kinematic outcomes, each participant’s ‘closeness’ to age-matched normative data will be calculated. This will then be compared between groups using a general linear model with the stratification factors included as fixed effects. This data will also be presented graphically via scatter and distributional graphs to describe the deviations from the normative data.

For all the measures of movement listed, a general linear model with the stratification factors included as fixed-effects will be used to assess for between-group differences. If appropriate, adjusted analyses will be undertaken by including baseline factors and fixed effects in the above models.

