### Analysis population and missing data

The analysis population is defined as:
Intention-to-treat: all randomised individualsPer-protocol: all randomised individuals who do not have an alternative TKR during the follow-up period. Individuals will be included up to the point of the alternative TKRSafety population: all randomised individuals who receive the TKR

Missing outcome data will be multiple imputed to increase precision of the treatment effect estimates. Sensitivity analyses will be conducted to assess the impact of the multiple imputations and a complete case analysis will also be conducted. All imputations will be examined to ensure that sensible values are being generated. Imputation models will contain baseline measures, outcome measures and factors predictive of missing data.

No interim analysis is planned for this study.

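### Participants whose allocated implant is not used are put under the withdrawal rule, which implies that their 6-month OKS is not collected and conflicts with intention-to-treat

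*Protocol article*

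**What the plan says.** The Surgical procedures section of the protocol article allows a decision, before or during the operation, not to use the allocated device if in the surgeon's opinion "the patient is found to have become unsuitable for continued participation in the trial". The reasons are recorded on the trial database. The section then gives its rule for keeping data: "In this case or if a participant chooses to withdraw consent for treatment, or follow-up, all data collected up to the point of withdrawal" is kept. One sentence therefore covers both the surgeon's decision not to use the device and the participant's own withdrawal of consent.

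The analysis sections say something different. Under Statistical analysis, "all participants will be analysed according to the group to which they were allocated, regardless of compliance". Under Analysis population and missing data, the intention-to-treat set is everyone randomised, and the per-protocol set is "all randomised individuals who do not have an alternative TKR during the follow-up period". The same section says: "Missing outcome data will be multiple imputed to increase precision of the treatment effect estimates". Sensitivity analyses and a complete-case analysis are added.

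Three other places bear on the point:

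- Blinding (masking): "It is not possible to blind the surgeon to the trial intervention".
- Allocation: randomisation takes place 4 days (± 3 days) before the operation, so the device decision comes after allocation.
- Informed consent and Sample size: if someone withdraws before surgery, "an additional participant will be randomised to ensure that 80 participants complete the surgery", whereas the sample-size text says "80 participants will be randomised to one of the two groups".

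**The concern.** In an implant trial, not receiving the allocated implant is the main form of non-compliance. Intention-to-treat needs the outcomes of exactly these participants. If non-use ends follow-up, the principle holds in name only: the participant is counted in the allocated arm, but the 6-month value is a model prediction.

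The decision is made after randomisation, at the surgeon's discretion and with the allocation known. Loss of outcome data triggered in this way need not be alike in the two arms. GENESIS II is the standard implant at both hospitals and has been used by these surgeons for many years (Surgical flow and training), so it is a plausible fallback when the other device is set aside. If that led to more non-use in one arm, and those patients would have done worse, the observed patients in that arm would look better than the arm as randomised.

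**Working it through.** **1. Does the text imply that follow-up ends?** Two features of the Surgical procedures section point that way. The trigger is unsuitability to continue in the trial, not merely unsuitability for one device. The sentence on keeping data ties non-use to the same cut-off as consent withdrawal. The decision falls at or before surgery and the primary outcome is measured 6 months after it, so a cut-off at the decision leaves only baseline data. No section of the article says that these participants continue to be assessed.

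**2. Set against the analysis sections.** Everyone randomised is in the intention-to-treat set, so nobody leaves the analysis population. Without a 6-month OKS, however, the value must be imputed. If follow-up ends for every participant whose device is not used, no such participant has an observed 6-month OKS. The imputation model can then learn the outcome only from patients who received their allocated device. Entering the recorded reason for non-use would not help, because there would be no observed outcomes to relate it to. The complete-case analysis drops these participants altogether. The per-protocol definition, which removes people with an alternative knee replacement, suggests that they are otherwise followed. It could also refer to a later re-operation, so it is supporting evidence only.

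**3. The plan's own figure.** Inputs from Sample size: difference 5, SD 7.4, power 80%, dropout 10%. Two-sided 5% significance is assumed, in line with the 95% confidence intervals in Statistical analysis.

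- Normal approximation: n = 2 × (1.96 + 0.84)² × 7.4² / 5² ≈ 34.4, so 35 per arm and 70 in total; 70 / 0.9 = 77.8, so 78.
- t-test: 35.4, so 36 per arm and 72 in total; 72 / 0.9 = 80.

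The stated 80 reproduces, so the sample size is not at issue.

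**4. Effect on power.** With 36 evaluable per arm, power by t-test is 80.7%. Losing a further 1, 2, 4 or 6 from one arm gives 80.1%, 79.5%, 78.2% or 76.8%. The loss is small.

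**5. Effect on the estimate.** Suppose x of 40 patients in one arm have no outcome and would have scored g points worse than the rest of that arm. The mean of the remaining patients then differs from the mean of the whole arm by (x/40) × g. Both x and g are assumptions; the document gives neither.

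| x of 40 | g = 5 | g = 7.4 (1 SD) | g = 10 |
|---|---|---|---|
| 1 | 0.125 | 0.185 | 0.25 |
| 2 | 0.25 | 0.37 | 0.50 |
| 4 | 0.50 | 0.74 | 1.00 |

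The range is about 0.1 to 1.0 point. As a share of the 5-point difference it runs from 0.125 / 5 = 2.5% to 1.0 / 5 = 20%. The table puts every loss in one arm and assumes that imputation recovers nothing; losses in both arms would partly cancel.

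**The case against.** The strongest reply is that the sentence is a retention clause. It says which data are kept and does not say that assessments stop. Where the protocol wants assessments to stop, it says so outright, as in Informed consent for participants who lose capacity. The Protocol amendments section also mentions a non-adherence and non-retention section of the full protocol, which is not shown and may set out follow-up after non-use. This stands to the extent that the end of follow-up is inferred, not stated. It does not remove the conflict, because the visible wording groups the two cases, ties both to a point of withdrawal, and is nowhere corrected.

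A reader might go further than the documents allow in three ways:

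- **That these patients are removed from the analysis.** They are not. The intention-to-treat set is everyone randomised, including anyone replaced before surgery.
- **That JOURNEY II will lose its difficult knees.** The rule covers both arms. Surgical flow and training reports minimal differences in technique, a shallow learning curve, and surgeons who practised until confident. The eligibility criteria already exclude marked fixed-flexion and uncorrectable varus/valgus deformity. Imbalance between arms is a possibility, not something the protocol states.
- **That the reason for non-use is barred from the imputation model.** It is recorded, and the plan allows predictors of missingness in the model. The difficulty is the absence of observed outcomes among these patients, not a restriction on covariates.

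It is also fair to say that nothing in the document indicates how often non-use would occur. Even the worst illustrative case needs 10% of one arm, each patient 10 points worse.

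**Conclusion.** The inconsistency is real and should be resolved, but it is a cheap improvement and not a defect that undermines the trial. As worded, the Surgical procedures section implies that participants whose allocated device is not used have no 6-month OKS, which does not fit the intention-to-treat commitment under Statistical analysis and under Analysis population and missing data. An analysis plan cannot repair this alone, because it cannot recover an outcome that was never collected.

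The possible bias is unknown in size and direction. The illustrative 0.1 to 1.0 OKS point rests on 1 to 4 losses out of 40, all in one arm, in patients who would have scored 5 to 10 points worse, with no recovery from imputation. Power is hardly affected.

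Separately, and of minor weight, the sample-size text fixes the number randomised at 80, while the replacement rule fixes the number completing surgery at 80. Any replacement takes the number randomised above 80.

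**What to change.** Reconcile the Surgical procedures section with the two analysis sections:

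- Treat non-use of the allocated device and withdrawal of consent for follow-up as separate events with separate rules.
- State that participants in the first group remain in follow-up unless they withdraw consent or lose capacity, have the 6-month OKS collected (by the telephone route already described under Outcomes if they cannot attend), and are analysed as randomised.
- Report the number of non-uses and the recorded reasons by arm.
- Align the Sample size wording with the replacement rule, for example at least 80 randomised so that 80 complete surgery.

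This concerns data collection and analysis only; the surgeon's choice of device is not in question. The cost is a wording change, a few extra questionnaire contacts, and slight dilution of the estimated effect by any crossovers, which is inherent in an intention-to-treat comparison. If the full protocol already provides for this follow-up, bringing the article's wording into line is enough.
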